### Patient follow-up and study endpoints

During the hospital course, patients will be visited every day by a cardiologist. Performed physical examinations and vital signs will be recorded. We will monitor the patients during admission and any signs of arrhythmia, pulmonary emboli, and coronary artery injury will be evaluated and recorded. Blood samples are drawn for measurement of fasting blood sugar (FBS), complete cell blood count (CBC), urea and electrolytes, liver function tests (LFTs), creatine kinase, and cardiac troponin T- and C-reactive protein. An electrocardiogram (ECG) test is also taken. Before the first cell infusion, cardiac magnetic resonance (CMR) imaging and echocardiography will be done. After cell infusion, patients will be discharged from the hospital with a prescription for beta-blocker, angiotensin-converting enzyme (ACE) inhibitor, aldosterone antagonist, aspirin, ticagrelor, statin, and nitrate spray or tablets to take as required and cardiac rehabilitation program. Blood tests, an ECG, and physical exams are again done at the 10th day (at time of admission for second cell infusion), 3-month, and 6-month visits. At the last visit, echocardiography and CMR will be re-performed. All the tests will be recorded.

The improvement in LVEF after 6 months will be the primary efficacy endpoint for this study. Secondary endpoints will be the infarct size of the infarcted and salvaged myocardium at 6 months as assessed by CMR, changes in LV function, left ventricular mass (LVM) index, left ventricular end diastolic volume (LVEDV), left ventricular end systolic volume (LVESD), and global longitudinal strain (GLS) at 6 months as determined by echocardiography.

### Cardiac MRI

CMR will be performed for each patient 3 days and 6 months after primary PCI. For evaluation of the ventricular function and volume of cine-CMR, and for determining the microvascular obstruction and size of the infarcted myocardium evaluation, delayed enhancement (DE)-CMR will be used. T2 imaging will be used to assess the myocardial salvage and infarct size. Optimization of myocardial nulling will be done by the inversion time. Images will be evaluated in a blinded way by an expert operator. Scar and edema volumes will be determined by manually tracing the endocardial and epicardial contours after semi-automated selection of the normal remote myocardium per slice.

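### Infarct size is assigned to both DE-CMR and T2 imaging, the 6-month salvage endpoint is not tied to the pre-infusion T2 scan, and the baseline scan is not used in the between-arm comparison of infarct size

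*Protocol article*

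**What the plan says.** All references are to the protocol article.

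- **Endpoints** (Patient follow-up and study endpoints): "Secondary endpoints will be the infarct size of the infarcted and salvaged myocardium at 6 months as assessed by CMR". Both quantities are dated to 6 months. Neither is worded as a change from the first scan.
- **Scan schedule.** The Cardiac MRI section states: "CMR will be performed for each patient 3 days and 6 months after primary PCI". The follow-up section adds: "Before the first cell infusion, cardiac magnetic resonance (CMR) imaging and echocardiography will be done", and "At the last visit, echocardiography and CMR will be re-performed". Each patient therefore has one scan before treatment and one at the end.
- **Sequence for infarct size, first statement** (Cardiac MRI): "size of the infarcted myocardium evaluation, delayed enhancement (DE)-CMR will be used".
- **Sequence for infarct size, second statement** (Cardiac MRI, next sentence): "T2 imaging will be used to assess the myocardial salvage and infarct size". It gives no time point.
- **What is traced** (Cardiac MRI): "Scar and edema volumes will be determined by manually tracing the endocardial and epicardial contours". Scar and oedema are named as two quantities.
- **Analysis** (Statistical analysis): one-way ANOVA followed by Tukey's test, for the change in LVEF and for the other outcomes. No covariate is named. Paired t-tests are planned within groups.

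**The concern.** Infarct size is a named secondary endpoint, and the article gives it two measuring sequences. T2 imaging marks oedema, which is used as the area at risk. Delayed enhancement marks scar. If T2 extent were recorded as infarct size, the salvaged zone would be counted as infarct. The value would be wrong, and readers following different sentences would record different quantities.

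Salvage needs two inputs, an area at risk and an infarct size. Oedema after infarction is an acute signal, so the area at risk has to come from the early scan. The article dates the endpoint to 6 months and assigns it to T2 without saying which scan supplies T2.

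The third matter is efficiency. Every patient is scanned before the first infusion, but the planned between-arm comparison of 6-month infarct size makes no use of that scan. In small arms, chance differences in initial infarct size then carry into the result.

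**Working it through.** The article gives no figure for these endpoints, so there is none to reproduce. The first two steps compare the text with itself; the third is a short calculation.

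**1. Infarct size.** The DE-CMR sentence and the T2 sentence stand next to each other and both claim infarct size. The later sentence on tracing separates scar from oedema, so the authors themselves treat them as different volumes. DE-CMR fits scar and T2 fits oedema. The mention of infarct size in the T2 sentence therefore conflicts with the sentence before it and with the tracing sentence.

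**2. Salvage.** Salvage = area at risk − infarct size. Two derivations are compatible with the schedule:

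| Area at risk from | Infarct size from | Sound? |
|---|---|---|
| Pre-infusion T2 | 6-month DE-CMR | Yes |
| 6-month T2 | 6-month DE-CMR | No, the acute oedema is no longer there to be measured |

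No sentence chooses between them. The first is available because the early scan is scheduled for every patient. The article does not state whether T2 is acquired at 6 months at all.

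**3. Chance imbalance at baseline.** Inputs: 20 per arm (Sample size determination; Intervention), and no stratification factor named (Randomization and study blinding). In units of the between-patient SD of pre-infusion infarct size, the standard error of the difference between two arm means is

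SE = √(1/20 + 1/20) = √(2/20) = 0.316.

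By the normal approximation, for one given pair of arms:

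- P(|difference| > 0.3 SD) = 2 × [1 − Φ(0.3/0.316)] = 2 × [1 − Φ(0.949)] ≈ 0.34
- P(|difference| > 0.5 SD) = 2 × [1 − Φ(0.5/0.316)] = 2 × [1 − Φ(1.581)] ≈ 0.11

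How much of an imbalance reaches the 6-month comparison depends on the correlation ρ between pre-infusion and 6-month infarct size. The documents do not give ρ, so it is left as a symbol. With equal SDs at the two scans, an imbalance of d SD shifts the unadjusted 6-month difference by ρ × d SD. Relative to the unadjusted 6-month comparison, the variance is about

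- 1 − ρ² with ANCOVA
- 2(1 − ρ) with a change score

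Since 2(1 − ρ) − (1 − ρ²) = (1 − ρ)² ≥ 0, ANCOVA does at least as well as a change score for any ρ. It also does at least as well as the unadjusted value, apart from the small cost of estimating one slope.

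**The case against.** The strongest reply is that the article does not prescribe the faulty derivation. A reader might infer that the salvage endpoint must give wrong values, coming out near zero or negative because oedema has resolved by 6 months. That requires T2 to be read from the 6-month scan, and no sentence says so. The 6-month date attaches to the endpoint, not to each of its inputs. The 3-day scan can supply the oedema extent, DE-CMR can supply the scar, and both volumes are traced. This part of the reply stands. Any numerical example of a negative salvage value would rest on assumed inputs under an unstated reading.

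A reader might also infer that salvage cannot reflect a treatment effect, because reperfusion came before the first infusion. The documents do not support that either. The area at risk is fixed before treatment, but the 6-month scar can still differ between arms.

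A further reply is that this is a condensed article, and that formulas and reading rules usually sit in a full protocol, imaging manual or analysis plan. That holds for a missing salvage formula taken alone. It does not cover the T2 sentence, which is a stated rule in conflict with its neighbour.

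On adjustment, the reply is that an unadjusted comparison is unbiased under randomisation, and that the ANOVA sentence might be read as using changes for the other outcomes too. The first half is correct, so the gain is in precision only. The second half is possible, but the endpoint is worded as a 6-month value, and a change score is in any case no more efficient than ANCOVA.

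**Conclusion.** The point holds as a conflict in wording and a missed gain in precision, both confined to secondary endpoints.

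- **Infarct size:** the double assignment is in the text and should be corrected. T2 extent is not infarct size.
- **Salvage:** the text allows a sound value but does not fix it. It cannot be said that the endpoint gives wrong values as specified.
- **Baseline:** the planned between-arm comparison of infarct size leaves the pre-infusion scan unused. For a given pair of arms, the chance of an imbalance above 0.3 SD is about 34%, and above 0.5 SD about 11%. This is noise, not bias. The precision gained by adjustment depends on a correlation that the documents do not give.

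The conclusion rests on general imaging knowledge that T2 shows transient oedema and delayed enhancement shows scar. The article does not state this, though its separate tracing of the two agrees with it. The probabilities assume 20 analysed patients per arm and the normal approximation.

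**What to change.** 1. In the Cardiac MRI section, remove infarct size from the T2 sentence, so that DE-CMR alone measures infarct size at both scans.
2. State that the area at risk for salvage comes from the T2 images of the pre-infusion scan and not from the 6-month scan, and that salvage is this area minus the 6-month DE infarct size.
3. In the Statistical analysis section, compare 6-month DE infarct size between arms by ANCOVA, with pre-infusion DE infarct size as covariate.

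These changes should be made before the blinded readings are finalised, so that the choice of sequence, scan and model cannot depend on the results.

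The cost is wording and one covariate. No scan is added, because CMR before the first infusion is already scheduled for every patient. That T2 and delayed enhancement are both acquired then is implied by the section rather than stated, and should be confirmed. The small downside is that a patient with an unreadable pre-infusion scan has no salvage value or no covariate. If a full protocol or analysis plan already defines salvage, item 2 only needs to be brought into line with it; item 1 is still needed.

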### Echocardiography

For evaluation of LV systolic function, echocardiography will be performed. By using wall motion score and Simpson’s rule, EF will be calculated. LV function will be evaluated on the day of hospitalization before cell infusion and 6 months after cell infusion to determine the changes in EF. GLS will be measured using automated formulas in standard views.

### Adjudication of potential endpoints

All measurements will be evaluated and judged by an independent, blinded expert. In the case of poor recordings, the expert chooses whether the measurement has adequate quality to be used for endpoint assessment or not. Measurements of inadequate quality will not be used in the analysis as missing measurements. Potential major adverse cardiac events (MACE) will be evaluated by an independent, blinded safety committee. All laboratory data and adjudications will be finalized and moved into the computer database prior to unblinding study.

### Statistical analysis

All data will remain anonymous before the analysis, which will be done by an independent, expert member of the department not involved in the trial. Based on the findings from previous meta-analysis, a 3% improvement in ejection fraction, as measured by CMR after 6 months, will be considered significant [26]. An intention-to-treat analysis will be performed. We will also analyze the baseline demographic and clinical characteristics for each arm of the study. Mean and standard deviation will be used for continuous variables, and categorical data will be shown by frequencies and percentages. One-way analysis of variance (ANOVA) will be used to perform comparisons of LVEF changes after 6 month (primary endpoint) and also other outcomes between the treatment arms regarding the followed by post hoc Tukey’s test for comparisons of the double-doses-infusion arm with single-dose-infusion group and placebo control-treated groups individually. Only cases with complete follow-up will enter the final analysis. Paired *t*-test will be performed for within-group comparisons. Estimated treatment effect will be reported with 95% CI. All *p* values will be two-sided. Safety events such as the incidence of MACE (death, recurrent AMI, ICD insertion, non-target vessel revascularization…) and serious adverse events (SAE) will be compared among the three arms, and Kaplan-Meier curves will be used to show the pattern of events during the 6-month follow-up. Using Cox’s proportional hazards model, statistical significance and 95% CIs will be reported.

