### Sample size determination

According to the objectives and type of the study and citing previous studies in this field, taking into account the 5% error, 90% power, 3% difference between placebo group and single dose injection group, and another 3% difference between single and double injection groups after the 6 month follow-up period and 1.3 standard deviation and 1:1:1 ratio, the sample size will be estimated in each group using the formula $$ n=\frac{2{s}^2{\left({z}_{1-\raisebox{1ex}{$\alpha $}\!\left/ \!\raisebox{-1ex}{$2$}\right.}+{z}_{1-\beta}\right)}^2}{{\left(\partial \right)}^2} $$ . Due to the length of the study and repeated measurements, using the formula $$ {n}^{\prime }=n\times \frac{1}{1-p} $$, and a drop of 15%, the sample size is decided 16 in each group. Finally, considering that in this study, three groups will be compared and according to the formula, $$ {n}^{\prime }=n\times \sqrt{k} $$, 20 subjects will be needed in each group, so a total of 60 patients will be selected. In the above formula, the values of *z* are constant and equal to 97.5th percentile and 80th percentile of the standard distribution. The ratio of people in the two groups and the effect size are the value divided by the standard deviation.

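### Baseline LVEF is left out of the primary analysis, the pairwise contrasts do not match those used to size the trial, and the 3% sentence blurs relevance with significance

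*Protocol article*

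**What the plan says.** All references are to the protocol article.

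- **Model.** Statistical analysis: "One-way analysis of variance (ANOVA) will be used to perform comparisons of LVEF changes after 6 month (primary endpoint". No covariate is named. Patient follow-up and study endpoints schedules both CMR and echocardiography before the first infusion and again at the last visit, so a baseline LVEF is planned for every patient.
- **Contrasts analysed.** The ANOVA is followed by Tukey's test for "comparisons of the double-doses-infusion arm with single-dose-infusion group and placebo control-treated groups individually". That is two pairs: double versus single, and double versus placebo.
- **Contrasts sized.** Sample size determination starts from a "3% difference between placebo group and single dose injection group". For the step from one dose to two, its assumption reads: "another 3% difference between single and double injection groups after the 6 month follow-up period and 1.3 standard deviation and 1:1:1 ratio". That is also two pairs, but a different two: single versus placebo, and double versus single.
- **The 3% sentence.** Statistical analysis says that "a 3% improvement in ejection fraction, as measured by CMR after 6 months, will be considered significant". The same section plans 95% confidence intervals, says that p "values will be two-sided", and adds paired t-tests within each arm.

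**The concern.** There are three separate points.

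1. A change score subtracts the baseline with a fixed coefficient of 1. ANCOVA estimates the coefficient and is never less efficient, apart from one degree of freedom. In a trial of 20 per arm, whose central question is a 3-point difference between two active arms, precision already in the data should not be left unused without a reason.
2. Tukey's method adjusts for all three pairs, the text names two, and the sample size section plans on one that is not named. As written, a reader cannot tell whether single versus placebo belongs to the confirmatory family.
3. The 3% sentence does not say what the improvement is measured against. Patients enter with LVEF below 40% within 3 to 7 days of infarction, and all receive standard treatment. A rise from baseline can therefore occur in any arm, controls included, so the comparator has to be stated.

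**Working it through.** **Inputs from the protocol.** Difference 3 points, SD 1.3, two-sided 5% error, 90% power ("taking into account the 5% error, 90% power"), 15% loss, 16 and then 20 per group. The section also describes the z values as "equal to 97.5th percentile and 80th percentile of the standard distribution", which is 80% power. With 20 per arm and 15% loss, 20 × 0.85 = 17 complete per arm, so the residual degrees of freedom are 3 × 17 − 3 = 48.

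**Assumptions (not in the protocol).** Correlation ρ between baseline and 6-month LVEF of 0.3 to 0.7; ratio k of baseline SD to 6-month SD of 1, or 0.6 if the entry limit narrows the baseline spread; the SD read as the SD of change.

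**Step 1. The protocol's own figure.** n = 2s²(z₀.₉₇₅ + z₀.₉₀)²/δ² = 2 × 1.69 × (1.960 + 1.282)²/9 = 3.95, so 4 per group. Dividing by 0.85 gives 5, and multiplying by √3 gives 9. At 80% power the steps are 3, 4 and 7. The stated 16 and 20 are not reproduced, and 16 × √3 = 27.7, not 20.

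**Step 2. The SD that the stated 16 implies.** Before loss, 16 × 0.85 = 13.6. Solving for s gives s = √(13.6 × 9/2)/3.242 = 2.41 at 90% power, or √(13.6 × 9/2)/2.802 = 2.79 at 80%. The protocol therefore supports two values: the stated 1.3, and about 2.4 to 2.8 from its sample size.

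**Step 3. Variance of ANCOVA relative to the change score.** In general this is (1 − ρ²)/(1 + k² − 2ρk). With k = 1 it reduces to (1 + ρ)/2.

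| ρ | k = 1 | k = 0.6 |
|---|---|---|
| 0.3 | 0.65 | 0.91 |
| 0.5 | 0.75 | 0.99 |
| 0.7 | 0.85 | 0.98 |

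The gain vanishes when ρ = k.

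**Step 4. Critical values at 48 degrees of freedom.** Tukey 2.418; two-contrast Dunnett 2.279; unadjusted 2.011. Using Tukey where only two contrasts are wanted costs about 8 to 9% in sample size.

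**Step 5. Power for one 3-point contrast, 17 per arm.** Power is from the noncentral t with noncentrality 3/(SD × √(2/17)), where the SD is multiplied by the square root of the Step 3 ratio for ANCOVA.

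| Method | SD 1.3 | SD 2.4 |
|---|---|---|
| Change score + Tukey (the plan) | about 100% | 88.5% |
| Change score + Dunnett | about 100% | 91.0% |
| ANCOVA + Tukey, k = 1, ρ 0.7 to 0.3 | about 100% | 93.3 to 98.0% |
| ANCOVA + Dunnett, k = 1, ρ 0.7 to 0.3 | about 100% | 95.0 to 98.6% |
| ANCOVA + Dunnett, k = 0.6, ρ 0.3 to 0.7 | about 100% | 91 to 94% |

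A simulation at SD 2.4, ρ = 0.5 and k = 1 agreed: 88.7% for change score + Tukey and 95.6% for ANCOVA + Tukey.

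At SD 2.79 the plan has 76%, against 87 to 94% for ANCOVA + Dunnett with k = 1.

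**Step 6. The 3% figure against the planned test.** The smallest observed difference that Tukey declares significant is 2.418 × SD × √(2/17). That is 1.1 points at SD 1.3, 2.0 at SD 2.4 and 4.2 at an assumed SD of 5. The 3-point figure and the test can therefore disagree in either direction, and one cannot stand in for the other.

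**The case against.** The strongest reply is that nothing is lost on the protocol's own figures. At SD 1.3 every method has about 100% power, and any loss needs a larger SD than the one stated. This stands for SD 1.3. It is weakened, though not removed, because the stated 16 per group cannot come from 1.3 and implies about 2.4. That discrepancy is a fault of the sample size calculation, not of the analysis model.

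Second, the ANCOVA gain is uncertain. Selecting on LVEF below 40% may narrow the baseline spread, and with k = 0.6 the gain nearly disappears. The narrowing may be only partial, since entry is judged by echocardiography while the 3% sentence refers to CMR. The objection limits the size of the gain, not its direction.

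Third, a reader might infer that Tukey pays for a contrast nobody tests. The document does not support this. The omnibus ANOVA spans all three arms, and the sample size section plans a single-versus-placebo difference. If that contrast is intended, Tukey is the matching adjustment. What stands is the mismatch between the two sections.

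Fourth, a reader might take the 3% sentence as a rule that declares success whatever the confidence interval, or expect a within-arm rise to be reported as efficacy. The text does not say either. It cites a meta-analysis for the figure, uses 3% as a between-arm difference when sizing the trial, promises p values and intervals, and ties the primary endpoint to the between-arm ANOVA. A relevant difference is the natural reading, so the fault is one of wording.

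**Conclusion.** The point holds as one of efficiency and coherence. A reader might infer bias from the unadjusted analysis. Under randomisation the change-score ANOVA is unbiased, and its standard error covers chance baseline imbalance.

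- **Baseline adjustment.** There is no measurable power loss at SD 1.3. At SD 2.4, with 17 completers per arm, the plan has about 88%, against about 95 to 99% for ANCOVA with two-contrast Dunnett under equal variances and ρ of 0.3 to 0.7, or about 91 to 94% if the baseline SD is 0.6 of the 6-month SD. The move from Tukey to Dunnett alone accounts for 2.5 of those points (88.5 to 91.0%). The values of ρ and k are assumptions.
- **Contrasts.** Sample size determination and Statistical analysis share only double versus single. This needs no assumption and must be reconciled.
- **3% sentence.** It is ambiguous as worded and should be corrected, but it is not shown to be a decision rule.

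The changes are worth making, but none is needed to make the trial valid.

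**What to change.** 1. Replace the ANOVA of change by ANCOVA of 6-month LVEF on arm and baseline LVEF, with both measured by the same modality. The cost is one degree of freedom and no new data.
2. Make the contrast family agree with Sample size determination. Either list all three pairs and keep Tukey, or, if only the two double-dose contrasts are wanted, use a two-contrast Dunnett-type adjustment and label single versus placebo as secondary. The second option takes a contrast used for sizing out of the primary family, so the sample size text would have to say so.
3. State 3 points as the clinically relevant difference between arms and nothing more. Base the conclusion on the adjusted contrast and its 95% confidence interval, and label the within-arm paired t-tests descriptive.

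All three are changes of wording, best made before unblinding.

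### Intention-to-treat is promised, but the final analysis admits only patients with complete follow-up, so the primary LVEF comparison becomes a completers analysis under an ITT label

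*Protocol article*

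**What the plan says.** The protocol article's Statistical analysis section first sets the principle: "An intention-to-treat analysis will be performed". It then describes a one-way ANOVA on 6-month LVEF change, the primary endpoint, followed by Tukey comparisons of the double-dose arm with each of the other two. The next sentence reads "Only cases with complete follow-up will enter the final analysis". The same paragraph goes on to compare MACE, with death listed first among its components, and serious adverse events across the three arms by Kaplan-Meier curves and a Cox model.

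Three other sections bear on this:

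- **Adjudication of potential endpoints:** "Measurements of inadequate quality will not be used in the analysis as missing measurements".
- **Sample size determination:** loss is expected, and the calculation allows for it ("and a drop of 15%, the sample size is decided 16 in each group") before the final 20 per arm is reached.
- **Randomization and study blinding:** only the outcome assessors are blinded. The Intervention section gives the control arm conventional treatment alone.

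The article has no modified-ITT definition, no rule for a missing 6-month LVEF and no rule for patients who die before 6 months. It does not say why follow-up might be incomplete.

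**The concern.** The two sentences name different analysis sets for the same comparison. Intention-to-treat means all randomised patients in their assigned arm. The later sentence keeps only those who finish. An analyst must set one aside, and the article does not say which. Because the second is the operational rule and directly follows the primary test, following the text gives a completers analysis that would be reported as ITT.

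Randomisation protects the comparison of everyone randomised. It does not protect a comparison of those who remain, if remaining depends on how the patient fares and on the arm. Both are possible here. A patient who dies before 6 months has no 6-month LVEF and leaves the primary analysis. Patients and treating staff can know the arm, so withdrawal and attendance may differ between arms.

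The word final is also unqualified. Taken literally, the rule would remove patients who died or were lost from the time-to-event safety analyses, the methods designed to use incomplete follow-up. A death excluded from a MACE comparison in a trial of 60 patients could change what that comparison shows.

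**Working it through.** **1. The plan's own loss figure**

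Inputs from Sample size determination: 20 per arm, 60 in total, 15% loss.

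- Excluded per arm: 20 × 0.15 = 3
- Excluded overall: 60 × 0.15 = 9
- Analysed: 17 per arm, 51 of 60

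The stated 16 and 20 per group do not follow from the stated inputs. The formula gives n = 2 × 1.3² × (1.960 + 1.282)² / 3² = 3.95, so 4 per group; 4 / 0.85 rounds up to 5. That is a separate matter. This point uses only the planned 20 per arm and the 15%.

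Inflating the sample for loss restores numbers. It does not restore comparability between the patients who remain.

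**2. The two rules side by side**

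| Patient | Under ITT | Under the complete-follow-up rule |
|---|---|---|
| Randomised, 6-month LVEF available | included | included |
| Alive, lost before 6 months | included, needs a missing-data rule | excluded |
| Died before 6 months | included, needs a rule for death | excluded from LVEF; literally also from Kaplan-Meier and Cox |
| Attended, 6-month scan judged inadequate | included, needs a missing-data rule | measurement is missing; the text does not say whether the patient counts as complete |

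The rules agree only in the first row.

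**3. How large a shift could be: assumed extreme case**

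Assume that LVEF change is normal, one arm loses exactly its worst 15%, and the other loses 15% at random. The first arm's completer mean then rises by

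φ(z₀.₁₅) / (1 − 0.15) = φ(−1.036) / 0.85 = 0.274 SD,

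and the second arm's does not move.

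| SD of LVEF change | Shift in arm difference | Share of 3-point target |
|---|---|---|
| 1.3 (stated in the plan) | 0.274 × 1.3 = 0.36 | 0.36 / 3 = 12% |
| 5 (assumed) | 0.274 × 5 = 1.37 | 1.37 / 3 = 46% |

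**4. A second illustration: unequal loss**

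Let g be the mean gap in LVEF change between completers and non-completers, and d the fraction lost. Each arm's completer mean overstates its full mean by g × d. With the same g in both arms, the arm difference shifts by g × (d₂ − d₁). Both g and the splits are assumptions.

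| Loss in the two arms | g = 3 | g = 5 | g = 10 |
|---|---|---|---|
| 15% and 15% | 0 | 0 | 0 |
| 10% and 20% | 0.3 | 0.5 | 1.0 |
| 5% and 25% | 0.6 | 1.0 | 2.0 |

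Neither calculation predicts the bias. They show that it can range from nothing to a sizeable part of the 3-point target.

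**The case against.** The strongest reply is that the sentences can be read together: intention-to-treat fixes the arm in which a patient is counted, and complete follow-up fixes who has an evaluable outcome. The result is an as-randomised complete-case analysis, which is weaker than ITT but not impossible. That reading is coherent, but the article does not state it, and such an analysis should not carry the unqualified ITT label. So the objection softens the charge of logical contradiction and leaves the mislabelling.

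It can also be said that a condensed article may leave missing-data detail to an analysis plan. That is fair for the imputation model. But the article does fix the analysis set, and does so in two ways.

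On safety, the plan does compare deaths and MACE across arms, so the authors probably did not intend the completers rule to reach those analyses. The wording still does not exclude them.

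A reader might go further and infer the following, which the document does not support:

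- **Losses will be outcome-related, mostly in patients with poor LVEF.** No reasons for loss are given. Only death is tied to a missing outcome by construction; withdrawal need not be.
- **ICD insertion will prevent a usable second CMR.** The article does not say so, and echocardiographic LVEF is also measured at 6 months.
- **Unreadable scans are selective.** Quality is judged by a blinded, independent expert, and nothing links it to arm or LVEF.
- **The second catheterisation removes double-dose patients.** Nothing says that a patient who misses the second infusion but attends at 6 months is incomplete.
- **The bias favours a particular arm.** The endpoint is change in LVEF. The sickest patients are not shown to have the smallest change, so no direction follows.

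**Conclusion.** The point holds as a defect in how the primary analysis set is defined. The text promises ITT and then prescribes completers only, without reconciling the two. At the planned 15% loss, about 9 of 60 randomised patients leave the primary analysis, including any who die before 6 months. The same wording, read literally, reaches the safety analyses.

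That some of these exclusions are related to outcome, or differ by arm, is possible but not established. The size and direction of bias cannot be derived from the document. The range of 0.36 to 1.4 points (about 12% to 46% of the target) rests on a deliberately extreme pattern of loss, and its upper end on an assumed SD of 5. If loss is equal and of the same kind in each arm, the shift is zero. The case for changing the text rests on the conflicting analysis set, not on a predicted bias, and it should be settled before unblinding.

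**What to change.** 1. Delete the complete-follow-up sentence as the primary rule. State that all randomised patients are analysed in their assigned arm, whether or not each infusion was given.
2. For survivors with a missing or unusable 6-month CMR LVEF (CMR is the modality that the Statistical analysis section names), use multiple imputation from arm, baseline CMR and echocardiographic LVEF, and 6-month echocardiographic LVEF where available. The 6-month echo carries most of the information; where it is also missing, imputation adds little beyond baseline adjustment. A mixed model alone would not help, because the plan has only one post-baseline LVEF time point.
3. Give deaths a separate pre-stated rule, for example a worst-rank sensitivity analysis. Do not impute an LVEF for a patient who has died.
4. Include all randomised patients in the Kaplan-Meier and Cox analyses, censored at last contact if event-free.
5. Keep the completers analysis as a labelled sensitivity analysis, and report the number and reasons for missing LVEF by arm.

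The cost is a wording change and modest extra analysis, with no new assessments. The drawback is reliance on a missing-at-random assumption for survivors, which the completers and worst-rank analyses help to probe.
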